### Eligibility criteria for sites and those delivering interventions {14b}

The trial will be conducted at the inpatient facility of a tertiary care centre, which provides clinical services for the management of addictive disorders. The intervention will be delivered by the primary investigator (first author) of the study, who holds a Master’s degree in Clinical Psychology and will be undertaking this randomized controlled trial as part of her doctoral thesis.

### Who will take informed consent? {32a}

Written informed consent will be obtained from participants fulfilling the inclusion criterion by the primary investigator after providing a verbal explanation of the participant information sheet and addressing all questions. Participants who indicate their willingness to take part in the study will then be provided with the written consent form (see Additional file 4) for review and signature.

### Additional consent provisions for collection and use of participant data and biological specimens {32b}

Participants will be informed during the consent process that the study involves the collection and analysis of deidentified clinical and behavioural data only, and that no biological specimens will be collected. Consent will include permission for the use of deidentified data for the purposes of generating findings of this research study, and no other additional studies in the future. Participants will be informed that their data will be stored securely, accessed only by authorised members of the research team, and that they may withdraw consent for data use at any time without affecting their ongoing clinical care.

## Intervention and comparator

### Intervention and comparator description {15a}

The training program which will be administered to the experimental group will be an associative Go/No-Go Paradigm with 100% contingency. It is a computerized behavioral intervention that leverages implicit processes to associate no-go responses with aggression-related stimuli, thereby developing habitual links with the goal of reducing aggressive behaviors. The go cues (pictures contained in circles) will be consistently paired with non-aggressive stimuli, and the no-go cues (pictures contained in squares) with aggressive stimuli, maintaining 100% contingency. Participants will be instructed to respond to stimuli in accordance with the format of the pictures. They will be directed to respond to pictures contained in circles by ‘pressing the space bar’ and to withdraw from responding to pictures contained in squares. The presentation of stimuli will be interspersed with brief intervals of 1000 ms (ms) featuring cross slides, termed ‘inter-trial’ periods. The intervention will be presented on Microsoft® PowerPoint for Mac (Version 16.78.3) software. The training program will be structured into six sessions, spanning three consecutive days, with two sessions delivered on each day. These sessions will progressively increase in complexity [28], in terms of reducing the probability of ‘No-Go’ stimuli and decreasing stimulus response duration (see Table 1).

**Table 1 Tab1:** Session-by-session plan for inhibitory control training

Training Session	Aggressive Stimuli (AS)		Non-Aggressive Stimuli (NAS)		Duration of Presentation (ms)	Total Time (Minutes)
	Proportion	Number [T (/C)]	Proportion	Number [T (/C)]		
Training Session—1	70%	35 (7)	30%	15 (3)	3000	15
Training Session—2	70%	35 (7)	30%	15 (3)	2500	15
Training Session—3	50%	25 (5)	50%	25 (5)	2500	15
Training Session—4	50%	25 (5)	50%	25 (5)	2250	15
Training Session—5	30%	15 (3)	70%	35 (7)	2250	15
Training Session—6	30%	15 (3)	70%	35 (7)	2000	15

*T (/C)* Total Pictures (Pictures Per Category), *ms* Milliseconds

Each session will consist of five blocks, and each block will comprise 50 trials. This structure will result in a total of 1500 trials throughout the training program. The choice of aggressive (no-go) and non-aggressive (go) stimuli employed in each training session will be determined by a Stimulus Evaluation Task, individualized to each participant [18].

The sham training administered to the control group will employ an associative Go/No-Go Paradigm with 50% contingency instead of 100% (see Fig. 2). Go and no-go cues will be split equally between aggressive and non-aggressive stimuli. Participants will receive the same instructions and the same method of presentation of the intervention. During the practice sessions, participants will not receive feedback on correct and incorrect responses. These sessions will not progressively increase in complexity, as shown in Table 2. The training will also be organized into six sessions, spread out over three consecutive days, with two sessions per day. Each session will consist of five blocks, and each block will comprise 50 trials. This structure will result in a total of 1500 trials throughout the training program. The choice of aggressive (no-go) and non-aggressive (go) stimuli employed in each training session will be determined by a Stimulus Evaluation Task [18].

**Fig. 2 Fig2:**
[figure not shown]
Panels represent the sequence of events during (**a**) Inhibitory Control Training and (**b**) Sham Training. The pictorial stimuli required for both training programmes shall be developed and validated in accordance with the Indian context for our target population

**Table 2 Tab2:** Session-by-session plan for sham training

Training Session	Aggressive Stimuli (AS)		Non-Aggressive Stimuli (NAS)		Duration of Presentation (ms)	Total Time (Minutes)
	Proportion	Number [T (/C)]	Proportion	Number [T (/C)]		
Training Session—1	50%	25 (5)	50%	25 (5)	3000	15
Training Session—2	50%	25 (5)	50%	25 (5)	3000	15
Training Session—3	50%	25 (5)	50%	25 (5)	3000	15
Training Session—4	50%	25 (5)	50%	25 (5)	3000	15
Training Session—5	50%	25 (5)	50%	25 (5)	3000	15
Training Session—6	50%	25 (5)	50%	25 (5)	3000	15

*T (/C)* Total Pictures (Pictures Per Category), *ms* Milliseconds

### Criteria for discontinuing or modifying allocated intervention/comparator {15b}

The allocated intervention or comparator will be discontinued if a participant withdraws consent, and no data from such participants will be included in the analyses. If a participant leaves the facility against medical advice (LAMA) or is discharged by the treating clinical team before completing the intervention schedule, the intervention will be discontinued; however, all data collected up to that point will be retained, and participants will be contacted for follow-up assessments, subject to their willingness to continue participation. However, there are no special provisions for modification of the intervention or comparator once allocated because the intervention is non-invasive and low risk, and therefore the requirement for individual modifications based on participant response or tolerability is not anticipated.

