#### Participant timeline {18}

Patients admitted to the National Drug Dependence Treatment Centre (NDDTC) will be administered upon a brief screening process. The screening will initiate only when the participant is able to actively engage in the study, ensuring they are not intoxicated or in a state of withdrawal. Withdrawal charting will be done using the Clinical Institute Withdrawal Assessment of Alcohol Scale, Revised (CIWA – Ar) [40] for alcohol, Clinical Opiate Withdrawal Scale (COWS) [41] for opioids, Minnesota Nicotine Withdrawal Scale (MNWS) [42], the Cannabis Withdrawal Scale (CWS) [43] for cannabis, and the Clinical Institute Withdrawal Assessment Benzodiazepines (CIWA—B) [44] scale for Benzodiazepines. If the participant is found intoxicated or experiencing withdrawal, the screening process will be paused. It will be resumed only after a reassessment of withdrawal symptoms has been conducted within the next 24–48 h.

Patients diagnosed with substance use disorder by a psychiatrist will then undergo the South Oaks Gambling Screen (SOGS) for the identification of problem or pathological gambling in the patients. Once it is ascertained that the participant fulfills the inclusion/exclusion criteria, written consent will be taken by the primary investigator, and patients will be randomized to either the experimental or control group. The Alcohol, Smoking, and Substance Involvement Screening Test (WHO-ASSIST Version 3.0) and the Overt Aggression Scale – Modified (OAS – M) will be administered along with the sociodemographic and clinical proformas. Other baseline assessments, including the Stimulus Evaluation Task, Inhibitory Control Task, and the Timeline Follow-Back Scale (TLFB) will also be performed post randomization. All questionnaires and assessments will be administered by verbally posing the questions (and options) to the patients. The demographic details, medical/psychiatric history of the participant, their family history, and treatment record will also be recorded (see Supplementary File 2).

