**Fig. 3 Fig3:**
[figure not shown]
Participant timeline: schedule of enrollment, interventions, and assessments

Written informed consent will be obtained from all the participants prior to enrolment by the primary investigator. No invasive procedure(s) will be conducted on the participants. All the information gathered in the course of the study will be kept confidential. Participation or non-participation in the study would not affect the usual treatment of the participants. The participants can withdraw their consent for participation in the study at any point. Participants will be informed that they will undergo either an active or sham training over three days, with assessments before, after, and during follow-ups at 1 and 3 months. Participation is voluntary, with no assured benefits or risks anticipated, and all data will be kept strictly confidential. While the intervention is intended to help, there is a possibility it may not produce the desired therapeutic effect. They will be informed that the sham training is designed to resemble the actual intervention without offering any therapeutic benefit.

During the course of study participation, any increase in distress or complaints noted or reported by the participant will be communicated to the treating team, and necessary referrals will be made. Any such adverse events occurring during the study period will be recorded and reported as per standard reporting guidelines.

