### Who will be included in each analysis {27b}

The primary analyses will follow the intention-to-treat (ITT) principle, including all randomized participants in the groups to which they were originally allocated, irrespective of intervention completion or follow-up attendance. In addition, per-protocol analyses will be conducted as a secondary analyses, including only participants who complete all six intervention sessions and all follow-up sessions.

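### The rule that no data from participants who withdraw consent are analysed conflicts with the stated intention-to-treat set of all randomised participants

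*Protocol article*

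**What the plan says.** All references are to the protocol article.

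- **Discontinuation criteria {15b}.** On withdrawal of consent, the allocated training "will be discontinued if a participant withdraws consent, and no data from such participants will be included in the analyses". The next sentence treats leaving against medical advice or early discharge differently: "all data collected up to that point will be retained, and participants will be contacted for follow-up assessments", if the participant is willing.
- **Analysis populations {27b}.** The primary analyses are ITT, "including all randomized participants in the groups to which they were originally allocated, irrespective of intervention completion or follow-up attendance". No exception for withdrawn consent is stated.
- **Consent for data {32b}.** Participants are told that "they may withdraw consent for data use at any time without affecting their ongoing clinical care". This is a right over the data.
- **Participant timeline {18}, text after Fig. 3.** "The participants can withdraw their consent for participation in the study at any point". This is a right over taking part.
- **Participant timeline {18}, order of events.** "written consent will be taken by the primary investigator, and patients will be randomized to either the experimental or control group", so consent comes before allocation.
- **Blinding {24a}.** Only participants are blinded. One investigator enrols, delivers the training, assesses outcomes and analyses.

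**The concern.** Two sections fix membership of the primary analysis set and give different answers for the same person. Section {15b} does not say which kind of withdrawal it means. As worded, a participant who simply no longer wants to take part is treated like one who forbids use of his data, although {32b} and {18} describe these as different things.

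An ITT set protects the randomised comparison because membership is settled at allocation. A rule that removes people for a later event gives up that protection. Here the event is also recorded by an investigator who knows the arm. A patient who leaves the ward and declines further contact keeps his data; one who stays on the ward and declines to continue could be recorded as withdrawing consent and lose all of his from the analysis. If the conflict is left open, the choice between the two rules could be made after the data have been seen.

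**Working it through.** **Step 1. Apply both sections to each event after allocation.**

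| Event | {15b} | {27b} | Result |
|---|---|---|---|
| Leaves against medical advice, or is discharged early | Data kept, follow-up attempted | Included | Agree |
| Misses sessions or visits, consent not withdrawn | No exclusion stated | Included | Agree |
| Withdraws consent to participate, says nothing about data | Excluded | Included | Conflict |
| Expressly withdraws permission for data use | Excluded | Included on the wording | Exclusion is defensible, but {27b} does not state it |

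The third row is the substantive fault. The fourth needs only a stated exception.

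**Step 2. Does the sample size absorb it?** The plan's figure reproduces: 26 / (1 − 0.60) = 65 per group, and 2 × 65 = 130. This inflation replaces lost numbers. It does not address who is lost, so it leaves the conflict as it is.

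**Step 3. How many people could be affected?** The documents give no rate of consent withdrawal. Assumed rates of 5%, 10% and 20% give 130 × 0.05 = 6.5, 130 × 0.10 = 13 and 130 × 0.20 = 26 participants removed from the ITT set.

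**Step 4. When does removal cause bias?** Assume no true effect. In each arm a share w withdraws, and withdrawers score s SD worse than that arm's overall mean. The remaining participants then have mean −w·s/(1 − w), and the spurious difference between arms A and B is

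s × [w_A/(1 − w_A) − w_B/(1 − w_B)],

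in favour of the arm with more withdrawals. The values of w and s below are assumptions; none comes from the documents.

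| Withdrawal, A vs B | Bracket | s = 0.5 | s = 1.0 |
|---|---|---|---|
| 5% vs 5% | 0 | 0 | 0 |
| 10% vs 5% | 0.1111 − 0.0526 = 0.0585 | 0.03 SD | 0.06 SD |
| 20% vs 5% | 0.2500 − 0.0526 = 0.1974 | 0.10 SD | 0.20 SD |

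The zero in the first row also requires withdrawers to be alike in both arms (same s).

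**Step 5. What part would retention recover?** The primary outcome is the change to 1 month. Someone who withdraws during the three training days leaves a baseline score and no 1-month score under either rule; retention keeps the baseline, but the outcome is still missing. Someone who withdraws after the 1-month visit has a primary outcome that {15b} discards and retention keeps. The table in Step 4 therefore describes the loss of withdrawers' outcomes in general. Only part of it is due to {15b}.

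**The case against.** **The sections can be read together.** The qualifying clause in {27b} names completion and attendance, not consent, so {15b} could be the specific exception that honours {32b}. This stands in part: leaving out data whose use has been forbidden is proper. But {27b} states no exception, and {15b} is not limited to data-use permission. The article says its analysis plan is integrated in the protocol {5}, so it points to no other place where the two are reconciled. The consent form (Additional file 4) is not shown and may draw the distinction.

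**Ordinary drop-out is already handled.** This stands. A reader might infer that everyone who stops training or is lost to follow-up is removed. The second sentence of {15b} and the wording of {27b} say otherwise.

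**Bias is conjecture.** This stands as to size. There are reasons why withdrawal could differ by arm: presentation shortens from 3000 to 2000 ms in the active arm and stays at 3000 ms in the sham arm (Tables 1 and 2), and the active arm uses the highest-rated aggressive pictures while the sham arm uses the lowest-rated ones. But the harms section {17} mentions only potential minor effects, and both arms have six sessions and 1500 trials. Nothing in the documents shows that withdrawal will differ.

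**The per-protocol set.** A reader might extend the point to the per-protocol definition, "including only participants who complete all six intervention sessions and all follow-up sessions". That is a secondary analysis, does not turn on consent, and is coherent with a model over four time points. It contradicts nothing and is not part of this point.

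**Conclusion.** The contradiction is real and needs no assumed figure: a participant who withdraws consent after allocation cannot be both left out of the analyses and included in the ITT set. It is limited to withdrawal of consent. Following {15b} would drop data already collected for a post-randomisation reason, and the result could not properly be called ITT.

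Three stronger readings go beyond the text:

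- **That the comparison is biased.** Bias needs withdrawal related to arm and outcome. It is a risk of unknown size: zero with equal withdrawal and like withdrawers, and 0.03 to 0.20 SD under the unequal rates assumed above.
- **That the bias can be stated as a share of the planned effect of 0.70.** That figure is a paired pre-post effect {19}, not a difference between arms, so it is the wrong yardstick.
- **That the data are erased.** The text says only that they are not analysed. The effect on the analysis set is the same.

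**What to change.** 1. In {15b}, separate two acts. When a participant stops training or follow-up, retain the data collected to that date and analyse them under ITT, with later outcomes treated as missing. Exclude data only when permission for their use is expressly withdrawn, as {32b} allows.
2. In {27b}, state that single exception, and report the number and timing of such exclusions by arm.
3. Check that the consent form distinguishes the two kinds of withdrawal.

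The cost is a sentence or two in each section and the consent-form check, made through the amendment route in {31}. Enrolment is expected to finish in December 2026 and analysis follows data collection, so the rule can be settled before any analysis. The change will not recover 1-month scores of participants who leave earlier; those remain a missing-data question.

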### Strategies to improve adherence to intervention/comparator {15c}

Adherence to the intervention and comparator protocols will be facilitated by conducting the study in an inpatient setting, allowing for scheduled and in-person delivery of all sessions. Sessions will be administered at pre-specified times, and participants will receive verbal reminders prior to each session. Attendance and completion of sessions will be recorded by the intervention provider. All six intervention sessions will be delivered in person by the primary investigator, who will directly monitor adherence during the intervention phase. Following discharge, the primary investigator will contact participants and their designated family members using previously obtained contact details to remind them of upcoming follow-up assessments during the week preceding each scheduled follow-up.

### Concomitant care permitted or prohibited during the trial {15d}

All participants will continue to receive treatment as usual (TAU) for addictive disorder, as decided by the treatment team. TAU may include pharmacotherapy, brief psychosocial interventions, and supportive care. No aspects of standard clinical care will be withheld or restricted due to trial participation.

### Ancillary and post-trial care {34}

No specific ancillary or post-trial care beyond routine clinical management is planned as part of this study. Participants will continue to receive standard treatment services at the study site irrespective of trial participation or completion. As the intervention is non-invasive, low risk and exploratory in nature, no trial-specific compensation has been planned. In the event of any distress or adverse experience related to trial participation, appropriate clinical support and referrals will be provided by the treating team at no cost to the participant.

### Outcomes {16}

#### Study instruments for primary outcomes

The Overt Aggression Scale‐Modified [29, 30] is a semi-structured interview designed to evaluate various categories of aggressive behaviors. Four sub-components make up the overall aggression (AGG) score: Verbal Aggression, Aggression Against Object, Aggression Against Others, and Aggression Against Self. Subcomponent scores are determined by multiplying the number and severity level of aggressive behaviors of each type during the prior week. Additional scores include a Global Anger and Aggression (GAA) score composed of two item ratings: Subjective experience of anger and overt expression of anger. The OAS‐M has been shown to be reliable and valid, with good psychometric properties in terms of internal consistency, inter-rater reliability, test–retest reliability, face validity, convergent validity, divergent validity, and discriminant validity [30]. The primary outcome of the study will be the change in overall aggression score from baseline to the 1-Month post-intervention follow-up, as measured using the Overt Aggression Scale–Modified (OAS-M), and will be summarized using mean values and standard deviations.

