Subsequently, the experimental and control group participants will undergo the inhibitory control training or sham training for 3 consecutive days, respectively, administered by the primary investigator (psychologist) for all patients. Throughout this period, the study participants will continue to receive concurrent treatment as usual as per the advice of the clinical treating team. Any changes in the medication that occur during the study period will be recorded.

One day after the intervention, participants will be assessed using the outcome measure administered during the baseline assessment. The first follow-up will be held at 1 month post-intervention (± 4 Days), and the second follow-up will be held at 3 months post-intervention (± 7). A comprehensive record of treatment prescribed to the participants will be maintained throughout the study period. After the final follow-up, participants will be prompted to guess their allocation group, either control or experimental, which will aid in assessing the effectiveness of the trial's blinding. They will also be asked about their perception of whether the intervention they received influenced their levels of aggression. The instrument administration and study timeline has been summarized in Fig. 3.

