## Data collection and management

### Plans for assessment and collection of outcomes {25a}

The outcome measures will be assessed at four time points: baseline (pre-intervention), 1-day post-intervention, 1-month post-intervention, and 3-months post-intervention. Pre-specified assessment windows have also been defined as follows: post-intervention (1 day), 1-month follow-up (± 4 days), and 3-month follow-up (± 7 days). All assessments will be administered by the primary investigator using standardized instruments, including the Overt Aggression Scale – Modified (OAS-M), Inhibitory Control Task, South Oaks Gambling Screen (SOGS), Alcohol, Smoking and Substance Involvement Screening Test (ASSIST v3.0), Timeline Follow-Back (TLFB), and the Stimulus Evaluation Task. These instruments have acceptable reliability and validity, with details of their psychometric properties described in the Methods section. To ensure consistency in questioning, questionnaires will be administered in Hindi following standardized translation procedures. All questionnaires will be asked in-person using an interview-style format with all participants to ensure that the data is complete and accurate. Data collection forms can be made available upon reasonable request to the corresponding author via email ([contact]).

The semi-structured proformas to be used in this study have been added to Additional file 3. The questionnaires for the Stimulus Evaluation Task, the Inhibitory Control Task, and the Inhibitory Control Training will be specifically developed for use in this study. Other questionnaires developed by other researchers to be employed in this study will also be appended to the same file—These questionnaires were either free to use or permission to use them in our study has been obtained from their authors.

Separate data collection forms will be created for baseline and for each follow-up time point. All data collection forms will be prepared using Microsoft® Word for Mac (Version 16.104) and stored in individual Word files for every participant. All assessments will be conducted in person by the primary investigator using an interview format. Questionnaires will be checked for completeness at the time of administration, allowing any missing or unclear responses to be clarified immediately.

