## Statistical methods

### Statistical methods for primary and secondary outcomes {27a}

Initial analyses will summarize demographic and clinical data of the participants using descriptive statistics. Mean values and standard deviations will be used to describe baseline and outcome variables for the experimental as well as for the control condition across all assessment times. Prior to further analyses, t-tests (or equivalent non-parametric tests) will be applied to confirm equivalence between both groups in demographic characteristics and pre-intervention scores. Any initial differences will be considered for adjustment in subsequent analyses. Based on the normality of the data, parametric or equivalent non-parametric tests will be conducted to assess the differential effects of the intervention training compared to the sham training on each outcome variable over time. The primary outcome, overt aggression measured using the Overt Aggression Scale – Modified (OAS-M), will be analysed with time (baseline, 1-day post-intervention, 1-month post-intervention, and 3-month post-intervention) as the within-subjects factor and group (inhibitory control training vs sham training) as the between-subjects factor.

Secondary continuous outcomes will also be analysed using similar models. Outcomes expressed as categorical or binary variables (e.g., substance use or gambling presence) will be summarised as frequencies and proportions and analysed using appropriate analysis methods. All statistical analysis methds wil onl;y be decided upon once its ensures that our collected data meets the assumptions of the respective test. Harms will be reported descriptively.

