### Methods for additional analyses (e.g. subgroup analyses) {27d}

After the completion of data collection, the data will be reviewed for suitability of the following analyses: Post hoc comparisons may be conducted for detailed analysis through between group and within group measures in case prior statistical analysis indicates significant differences. The moderating effect of changes in inhibitory control and stimulus devaluation immediately post intervention on changes in overt aggression behaviours at 1-month and 3-months post-intervention may be analysed.

The moderating effect of changes in inhibitory control and aggressive behaviour immediately following the intervention and at 1-month post-intervention on changes in substance use frequency and gambling behaviour at 1-month and 3-months post-intervention may be analysed.

If a significant dropout rate occurs during the study, an analysis can be conducted to identify any patterns or trends in the characteristics of participants who dropped out. This analysis can help understand potential reasons for dropout in terms of demographic, clinical, or other factors associated with higher dropout rates.

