### Expected limitations and strengths

Among the strengths of the study is the use of a randomized controlled trial design that incorporates permuted block randomization and allocation concealment through the SNOSE method with well-structured active and placebo interventions. Another strength is the application of sham training on the control group which while controlling for time and attention, might also provide information into the underlying mechanism of functioning of this intervention. The use of multiple validated outcome measures ensures that all behavioural dimensions will be accurately recorded. Questionnaires are also being translated into Hindi, to maintain the consistency of questioning. Furthermore, assessments across four time points, including follow-ups at one-day post intervention, allow the investigation of both immediate and sustained effects. The individualized stimulus selection based on participant ratings may increase personal relevance, potentially increasing its effectiveness. Furthermore, the toolbox and the intervention prepared for this study can also be validated and applied on different populations, and for different treatment interventions.

However, along with the strengths, the limitations of the study must also be acknowledged. The study sample will be restricted to male inpatients with a specific diagnosis, which might limit its applicability to other populations. The same is the case with the development and validation of the study intervention. The intervention itself is brief, lasting only 3 days, and based on inconclusive mechanisms of work, which raises questions about its capacity in being capable of dealing with complex, chronic patterns of behavior. Lastly, the computerized nature of the task, although practical, may not be completely representative of real-world interactions of aggressive behavior.

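### The 1-day OAS-M looks back a week, mostly to days before and during training, so it cannot be read as an immediate effect on aggression

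*Protocol article*

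**What the plan says.** All places are in the protocol article.

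- **Recall period.** Study instruments for primary outcomes: OAS-M subcomponent scores come from "multiplying the number and severity level of aggressive behaviors of each type during the prior week". The same section sets the primary outcome as the change in overall aggression score from baseline to 1 month.
- **Training.** Intervention and comparator description {15a}: "six sessions, spanning three consecutive days, with two sessions delivered on each day".
- **Visits.** Participant timeline {18}: at baseline "the Overt Aggression Scale – Modified (OAS – M) will be administered along with the sociodemographic and clinical proformas", and then "One day after the intervention, participants will be assessed using the outcome measure administered during the baseline assessment". Plans for assessment and collection of outcomes {25a} lists the OAS-M among the instruments and gives the windows as "post-intervention (1 day), 1-month follow-up (± 4 days), and 3-month follow-up (± 7 days").
- **Primary analysis.** Statistical methods {27a}: the OAS-M "will be analysed with time (baseline, 1-day post-intervention, 1-month post-intervention, and 3-month post-intervention) as the within-subjects factor", with group as the between-subjects factor. No single contrast is named as the test.
- **Additional analyses {27d}.** One optional analysis uses "changes in inhibitory control and aggressive behaviour immediately following the intervention", together with the same changes at 1 month, as moderators of later change in substance use and gambling.
- **Expected limitations and strengths.** The four time points, including the one-day follow-up, are said to "allow the investigation of both immediate and sustained effects".

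**The concern.** A scale that counts a week of behaviour is given one day after a three-day course, so most of what it records happened before the course was complete. Three uses of the score are at risk.

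1. **The 1-day comparison.** A true effect would be diluted, and a finding of no early change in aggression would say little.
2. **The shape over time.** A small group difference at 1 day and a larger one at 1 month would look like delayed onset, yet the recall window alone can produce that pattern.
3. **The predictor in {27d}.** Change in aggression from baseline to 1 day would largely reflect behaviour before and during training. If baseline is taken shortly before the first session, the two recall weeks may also share days. The gap between baseline and session 1 is not stated, so the extent of this overlap is unknown.

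**Working it through.** **Day count.** Inputs: a 7-day recall (Study instruments for primary outcomes), training on days 1 to 3 ({15a}), and the visit on day 4 ({18}). The text does not say whether the visit day counts, so both cases are shown.

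| Recall week | Before training | Training days | After training |
|---|---|---|---|
| Visit day counted (days −2 to 4) | 3 | 3 | 1 |
| Visit day not counted (days −3 to 3) | 4 | 3 | 0 |

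So 3/7 to 4/7 (43% to 57%) of the week precedes the first session, and at most 1/7 (14%) follows the last.

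**Share of the week that can carry an effect.**
- Effect starts only after the last session: 1/7 with the visit day counted, 0/7 without.
- Full effect from the first training day: (3 + 1)/7 = 4/7 with the visit day counted, 3/7 without.

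**At 1 and 3 months.** Even at the early edge of each window (4 and 7 days early), the recall week begins well after the last session. The declared primary contrast is clean.

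**Illustration of dilution.** Sample size {19} gives an effect size of 0.70. It reproduces as a paired, pre-post figure:

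- SD of the difference = √(3.89² + 1.92² − 2 × 0.5 × 3.89 × 1.92) = √(15.13 + 3.69 − 7.47) = 3.37
- Effect size = (3.44 − 1.07) / 3.37 = 0.70

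It is not a between-group effect at a visit. It is borrowed below as an assumed between-group effect, with behaviours spread evenly over days and an unchanged SD. Power is for a two-sided two-sample t-test at 0.05 with all 65 per arm seen at 1 day.

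| Assumed onset | Share | Effect at 1 day | Power |
|---|---|---|---|
| After the last session, visit day counted | 1/7 | 0.70 × 1/7 = 0.10 | 9% |
| First training day, visit day not counted | 3/7 | 0.70 × 3/7 = 0.30 | 40% |
| First training day, visit day counted | 4/7 | 0.70 × 4/7 = 0.40 | 62% |
| No dilution | 7/7 | 0.70 | 98% |

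**Does the extra level weaken the overall time-by-group test?** This was checked under equal variances and a correlation of 0.5 between visits, with no effect at baseline, a full effect (0.5 or 0.7) at 1 and 3 months, and 26 to 65 per arm. For 1-day shares of 1/7 to 4/7, keeping the level changes power by about −6 to +7 percentage points compared with dropping it. A heavily diluted level behaves like a second baseline and can even raise power. There is no consistent loss.

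**The case against.** The strongest reply is that the trial's main question is unharmed. The primary outcome is fixed at 1 month, and Expected outcomes looks for reduced OAS-M aggression mainly at 1 and 3 months. This stands.

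Several stronger readings are tempting, and the document does not support them:

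- **That the protocol rests its immediate-effect claim on the OAS-M.** The sentence under strengths speaks of assessments in general and does not name the scale. The Inhibitory Control Task and Stimulus Evaluation Task have no recall week and suit a 1-day visit.
- **That the score can show nothing at 1 day.** If the effect builds during training, up to 4/7 of the week carries some of it. The protocol does not say when an effect should start.
- **That the true 1-day effect would be 0.10 to 0.40 SD.** Those figures rest on a borrowed paired effect size and on assumptions about onset and spread.
- **That the 1-day level adds noise to the primary test, or could create a false effect.** The power check shows no consistent loss, and both arms share the same window, so the pull is mainly towards no difference.
- **That the visit should leave the model altogether.** Sample size {19} expects about 45% dropout by 1 month. For many participants the 1-day OAS-M may be the only value after baseline, and it can inform a repeated-measures or imputation model.

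Two further points in the plan's favour stand. The {27d} analyses are optional, and they already include 1-month aggression change. The supplementary outcome tables and the timeline figure are not shown and might define a different recall period.

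What the reply does not answer is that the text shown pairs a one-week recall with a one-day visit and then treats the result as a post-intervention level and as a possible measure of change straight after training.

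**Conclusion.** The point holds as a limit on interpretation, not as a fault in the primary endpoint. At the 1-day visit at most 1 of 7 recalled days follows training, and 3 to 4 precede it. Any group difference in OAS-M at that visit is diluted towards zero by an amount that depends on an unknown onset. It cannot be read as an immediate effect on aggression, and a contrast between 1 day and 1 month cannot be read as delayed onset. Change in aggression from baseline to 1 day is a contaminated predictor.

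The day count rests only on the stated recall period, training length and visit timing, and on no adapted recall period being set in material not shown. The size in SD units is illustrative only.

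**What to change.** 1. **Statistical methods {27a}.** Make the primary test the between-group difference in OAS-M at 1 month, adjusted for baseline OAS-M, in place of an overall test across four time levels. This also matches the declared primary outcome.
2. **1-day OAS-M.** Report it descriptively, state the recall period beside it, and draw no immediate-effect or delayed-onset conclusion. Allow it as auxiliary information in the repeated-measures or imputation model, given the expected dropout.
3. **Additional analyses {27d}.** Drop 1-day aggression change as a predictor. Use 1-month OAS-M change as the earliest aggression predictor, related to substance use and gambling at 3 months. The 1-day inhibitory control and stimulus devaluation measures can stay.
4. **Expected limitations and strengths.** Limit the claim about immediate effects to the Inhibitory Control Task and Stimulus Evaluation Task.
5. **Timing.** Record the date of baseline and of session 1 so that overlap of the recall weeks can be described.

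The cost is wording, plus two dates per participant if they are not already kept. All analyses are to follow completion of data collection, so the change can be made before then. The trial gives up a 1-day inference on aggression, which the instrument cannot support, and the possibility of relating 1-day aggression change to 1-month substance use and gambling.
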